### 2.11. Significance of the D-CURE Trial

If the efficacy and safety of UEMR are proven in this RCT, it is expected to be recognized as the standard treatment for SNADETs ≤ 20 mm. Owing to the absence of submucosal injection, UEMR is a simpler and more cost-effective technique compared to CEMR and is anticipated to become the primary method of EMR.

### 2.12. Data Collection and Management

After obtaining written consent from the patients, the investigators will reconfirm that the cases meet all inclusion criteria and do not meet any exclusion criteria. Subsequently, investigators who have been pre-registered in the D-CURE Electronic Data Capture (EDC) system will enter anonymized data into the web-based EDC system of the UMIN Internet Data and Information Center for Medical Research (UMIN INDICE). Changes made in the EDC will be recorded in a log, including information on who made the changes and when. The EDC system and associated databases will be secured and protected with specific passwords. The collected data will be stored online. However, if patients request data deletion after withdrawing their consent, their data will be deleted.

### 2.13. Planned Statistical Analyses

In this trial, the primary analysis will be conducted for the primary endpoint, the 1-year RFS, and this will be the final analysis. The analysis will be conducted within a year from the end date of final data collection of the registered cases by an independent biostatistician separate from the research physicians. Given the short planned registration and observation periods after protocol treatment, an interim analysis aimed at early termination will not be conducted.

The full analysis set (FAS) will consist of all enrolled patients who are randomized to the study arm, excluding some patients for the following reasons: violation of the eligibility/exclusion criteria, erroneous enrollment, no available data after randomization (e.g., withdrawal of consent), and failure to undergo EMR for SNADET. Cases in which the treatment protocol is changed or discontinued will be included in the FAS. The per-protocol set (PPS), a subset of the FAS, will exclude FAS cases with the following violations: incomplete protocol treatment and other serious protocol violations (e.g., treatment for SNADET exceeding 20 mm). The safety analysis set will include patients enrolled in this study whose treatment protocol is initiated and whose clinical course is followed for up to 28 days after the EMR. Cases in which protocol treatment has not been initiated will not be included in the safety analysis set.

#### 2.13.1. Analysis of Efficacy

The analysis of efficacy will be based on the FAS as the primary analysis population. A similar analysis will be conducted separately for the PPS. Subgroup analysis will also be performed according to preoperative biopsy status (present vs. absent), tumor length (<10 mm vs. ≥10 mm), and lesion location (bulb vs. other portions), which are allocation adjustment factors. Furthermore, an analysis of cases of untraceability (missing values) will be conducted, considering the inability to perform follow-up EGD.

Analysis of primary endpoint

The 1-year RFS, the primary endpoint, will be aggregated for each group, and the intergroup difference and the 95% confidence intervals (CI) will be calculated. The null and alternative hypotheses for the non-inferiority test are as follows:

Null hypothesis: 1-year RFS of UEMR, P1 + Δ ≤ 1-year RFS of CEMR, P2 (UEMR is inferior to CEMR by more than Δ)

Alternative hypothesis: 1-year RFS of UEMR, P1 + Δ > 1-year RFS of CEMR, P2 (UEMR is not inferior to CEMR by more than Δ)

If the null hypothesis is rejected at a one-sided 5% significance level in the non-inferiority test, we will conclude that UEMR is not inferior to CEMR. If non-inferiority in the 1-year RFS is demonstrated in the primary analysis, a test for superiority will be conducted.

2.Analysis of Secondary Endpoints
a.*En bloc* resection rate, histological complete resection rate, technical success rate, complete mucosal closure rate, and complete mucosal closure rate with standard clips: The rates for the CEMR and UEMR groups, the point estimate of the intergroup differences, and the 95% CI will be calculated.b.Total procedural, resection, and mucosal closure times: Summary statistics will be computed for both groups. The Wilcoxon rank-sum test will be used.c.One-year duodenum preservation survival rate: The rates for the CEMR and UEMR groups, the point estimate of the intergroup difference, and the 95% CI will be calculated.d.Device cost: Summary statistics will be computed for each group, and the Wilcoxon rank-sum test will be used for comparison.

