#### 2.7.5. Rescue Treatment in Case of Incompletion of Allocated Endoscopic Resection Method

If the allocated endoscopic resection method is attempted repeatedly and is not completed within 15 min from the beginning of treatment, the endoscopist may switch to an alternative treatment method, such as CEMR, UEMR, ESD, or surgical resection at their discretion. In this case, the protocol treatment will be discontinued, and the procedure will be considered a failure to achieve completion.

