#### 2.9.2. Secondary Endpoints

The secondary endpoints and their definitions are as follows:*En bloc* resection rate

The *en bloc* resection rate is defined as the proportion of cases in which complete removal of the lesion in a single piece without residual visible tumors is achieved, with the number of treated cases as the denominator. Cases in which resection is performed using methods other than the allocated EMR will be considered failures.

2.Histological complete resection rate

Resected specimens will be appropriately oriented and pinned onto a specimen board, such as a cork, before fixation in formalin. The histological complete resection rate is defined as the proportion of cases in which *en bloc* resection is achieved without histological tumor infiltration at the horizontal and vertical margins in the specimen. The number of treated patients will be the denominator.

3.Adverse events

The adverse event rate is defined as the proportion of patients with one or more expected or unexpected complications observed up to 28 days after EMR, with the treated patients as the denominator. Adverse events will be monitored and recorded as follows:

a.Intraoperative perforation

Intraoperative perforation is defined as a suspected perforation during EMR or the detection of free air on radiography or CT immediately after EMR.

b.Intraoperative bleeding

Massive intraoperative bleeding is defined as bleeding that occurs during EMR and requires interventional radiology or surgery.

c.Delayed bleeding

Delayed bleeding is defined as clinical findings of bleeding (hematemesis, melena, or a decrease in Hb by ≥2 g/dL) observed within 28 days after EMR and confirmed bleeding from the ulcer site after EMR by EGD. Gastric or duodenal blood retention and bleeding from the ulcer site after EMR observed during second-look endoscopy without the above clinical findings are not considered postoperative bleeding.

d.Delayed perforation

Delayed duodenal perforation is defined as perforation not suspected during the procedure and first recognized on the day following the completion of EMR or later.

4.Technical success rate

Technical success is considered when the lesion is completely removed using the allocated EMR method. The number of treated patients is the denominator.

5.Total procedure time

The total procedural time is calculated only for cases of successful resection (per-protocol analysis).

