A recent prospective observational study was conducted in Japan to evaluate the treatment of SNADETs ≤ 20 mm [12]. This study included 155 patients who underwent UEMR from multiple centers. The *en bloc* and histological complete resection rates were 89.8% and 66.9%, respectively, with a 1-year non-recurrence rate of 97.2%. However, our D-CURE trial has several strengths compared to previous studies. First, this is the first RCT conducted across 40 institutions in Japan, enabling the demonstration of safety and efficacy through random allocation and comparison, thus mitigating the possibility of selection bias observed in single-arm prospective trials. We aim to establish the efficacy, safety, and cost-effectiveness of UEMR based on robust results from the D-CURE trial. Additionally, the D-CURE trial includes mucosal closure as a component of the treatment protocol following resection. Mucosal closure has been shown to significantly reduce postoperative complications such as delayed bleeding and perforation by protecting the submucosal and muscular layers from bile and pancreatic juice. Although mucosal closure is considered essential, it is effective only when the ulcer bed is completely covered by the mucosa [34,35]. Although various closure methods using suturing devices have been reported, a simple and cost-effective method is preferred. Because the ulcer bed after UEMR tends to be smaller than that after CEMR, owing to the absence of submucosal injection, suturing with standard clips may be easier. Therefore, in this study, we specified a protocol to use standard clips as the primary method for closure. This approach may highlight differences in the complete mucosal closure rate achieved with standard clips between CEMR and UEMR.

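### Repeating technical success and en bloc rates in the per-protocol set is nearly circular, because that set drops patients who switched away from the allocated method

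*Protocol article*

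**What the plan says.** All references are to the protocol article.

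- **Section 2.13.1 (Analysis of Efficacy):** "The analysis of efficacy will be based on the FAS as the primary analysis population". Next comes "A similar analysis will be conducted separately for the PPS". Both sentences precede the primary and the secondary endpoint lists, and neither list exempts an endpoint. Secondary item a covers the en bloc, histological complete resection, technical success and two closure rates.
- **Section 2.13 (Planned Statistical Analyses):** for the FAS, "Cases in which the treatment protocol is changed or discontinued will be included in the FAS". The PPS, a subset of the FAS, "will exclude FAS cases with the following violations: incomplete protocol treatment and other serious protocol violations".
- **Section 2.7.5 (Rescue Treatment):** the endoscopist may switch method if the allocated one is not completed within 15 minutes. In that case "the protocol treatment will be discontinued, and the procedure will be considered a failure to achieve completion".
- **Section 2.9.2 (Secondary Endpoints):** "Technical success is considered when the lesion is completely removed using the allocated EMR method", and "The number of treated patients is the denominator". Resection by a method other than the allocated EMR counts as an en bloc failure. Histological complete resection requires en bloc resection.

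**The concern.** A per-protocol set is useful when membership does not depend on the outcome being compared. Here it does. A patient whose lesion could not be removed by the allocated method leaves the PPS for that reason, and the same event is what the technical success endpoint counts. A PPS table of technical success would show near-perfect rates in both arms whatever happened in the procedure room. A reader could take it for evidence of equal technical performance.

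En bloc and histological complete resection are affected less, because piecemeal resections completed with the allocated method stay in the PPS. Only the failures due to switching disappear. If one arm switches more often, that arm's rate rises more.

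Unequal switching is plausible on the article's own rationale. Section 1 says that poor mucosal elevation in CEMR can lead to piecemeal resection or conversion to ESD, and that UEMR can address this. The PPS would then remove some of the failures that UEMR is meant to avoid.

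**Working it through.** **Plan's own figure.** The sample size reproduces: with 97% in both arms, a 5-point margin, one-sided alpha 0.05 and 80% power, the requirement is 144 per arm, 288 in total, and 288 / 0.90 = 320. It rests on 1-year RFS and plays no part in what follows.

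**Technical success.** Let s be the share of treated patients in an arm who switch away from the allocated method. Assume that these are the only FAS patients the PPS removes.

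- FAS rate = 1 − s
- PPS rate = (1 − s) / (1 − s) = 100%, whatever s is

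There is one apparent exception. Section 2.7.3 permits additional cold snare, cold forceps or hot forceps excision of small residual lesions. Such a patient stays in the PPS, and the article does not say whether this counts as removal by the allocated method. If a share r of treated patients were counted as failures for this reason, the PPS rate would be 1 − r / (1 − s). No value of r is given. Switched cases remain excluded either way.

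**En bloc rate.** Every switched case is an en bloc failure, so all en bloc successes are in the PPS:

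- PPS rate = FAS rate / (1 − s)

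The article gives no switch rates, so s is assumed between 2% and 10%. The starting rates are those quoted in section 2.5 (Randomization) for 10–14 mm lesions, used as a stand-in for FAS results: CEMR 91.3%, UEMR 81.5%, difference (UEMR − CEMR) −9.8 points.

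| Switch rate CEMR / UEMR | PPS CEMR | PPS UEMR | PPS difference |
|---|---|---|---|
| 2% / 2% | 91.3 / 0.98 = 93.2% | 81.5 / 0.98 = 83.2% | −10.0 |
| 8% / 2% | 91.3 / 0.92 = 99.2% | 81.5 / 0.98 = 83.2% | −16.1 |
| 2% / 10% | 91.3 / 0.98 = 93.2% | 81.5 / 0.90 = 90.6% | −2.6 |

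With equal FAS rates of 90% (assumed), switch rates of 8%/2% give 90 / 0.92 = 97.8% against 90 / 0.98 = 91.8%. That is a difference of −6.0 points where the FAS shows none. Reversing the switch rates gives +6.0.

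**The same from the other direction.** Assume en bloc rates among completers of 94% (CEMR) and 90% (UEMR). The PPS difference is then always −4.0, while the FAS difference depends on switching:

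- 6%/2%: 0.94 × 94 = 88.4% v 0.98 × 90 = 88.2%, difference −0.2
- 2%/6%: 0.98 × 94 = 92.1% v 0.94 × 90 = 84.6%, difference −7.5
- 8%/2%: 0.92 × 94 = 86.5% v 0.98 × 90 = 88.2%, difference +1.7

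**Histological complete resection.** It requires en bloc resection, so the same factor 1 / (1 − s) applies to each arm.

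**The case against.** **The repeat may not cover the secondary rates.** Section 2.13.1 speaks only of a similar analysis. Section 2.9.2 fixes treated patients as the denominator for these rates and attaches a per-protocol label only to total procedure time and resection time. On that view the definitions govern, and the SAP, which is not shown, may already confine the PPS to the primary endpoint. This has some force, since the text does not say that every endpoint is repeated. It does not settle the matter: section 2.9.1 gives 1-year RFS the same treated-case denominator, and the PPS plainly applies there. The plain reading still takes in the secondary rates.

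**A rate of exactly 100% is not established.** A reader might infer that PPS technical success is 100% by definition. Section 2.13 does not define incomplete protocol treatment, and the permitted excision of residual tissue leaves a gap. This part of the objection stands: the supportable statement is close to 100%, provided such cases are few or count as successes.

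**Closure rates.** A reader might extend the point to mucosal closure, because the Discussion says "the D-CURE trial includes mucosal closure as a component of the treatment protocol following resection". The documents do not support that. Section 2.7.4 permits other closure devices and classes their use only as failure of standard-clip closure, and section 2.7.5 concerns the resection method. Nothing says that incomplete closure removes a patient from the PPS.

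**The en bloc shift is assumed.** This is true. The size and direction come from illustrative switch rates. An en bloc rate among patients who completed the allocated method is also a legitimate descriptive quantity if it is labelled as such.

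**Conclusion.** The point holds in limited form. Read plainly, the plan repeats secondary rates in a set selected on the outcome that one of them measures. PPS technical success would carry almost no information about the arms. The PPS en bloc difference moved by up to about 7 points in the scenarios shown (−9.8 to −2.6), but by only 0.2 points when both arms switched at 2%.

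This rests on three assumptions: that incomplete protocol treatment means a switch as described in section 2.7.5, that switched cases are the only PPS exclusions, and that switch rates lie in the assumed range.

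A reader might infer that the main conclusions are at risk. They are not. The FAS is the primary population and keeps changed or discontinued cases, so switch failures appear in the main secondary results. The secondary rates receive only estimates and confidence intervals. The primary non-inferiority test in the FAS does not depend on any of this. The severity is minor.

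**What to change.** State that the PPS analysis applies to 1-year RFS. Report technical success, en bloc resection and histological complete resection in treated (FAS) patients only, in line with the denominator in section 2.9.2. If an en bloc rate among completers is still wanted, label it descriptive and conditional on completing the allocated method.

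The cost is one sentence in the SAP. Sample size and trial conduct do not change, and fewer tables are needed. The only loss is the PPS version of these three rates.

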### 2.5. Randomization

A randomization process will be conducted using a central web-based system to assign patients to either the CEMR or UEMR group in a 1:1 allocation ratio. For random allocation, a minimization method will be used, incorporating four allocation adjustment factors that may influence the treatment outcomes of EMR. Allocation concealment will be ensured using a central web-based system, through which treatment assignments will be generated only after patient registration and confirmation of eligibility. Investigators and endoscopists will not have access to the allocation sequence in advance and will be unable to predict upcoming assignments.

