#### Randomization Adjustment Factors and Their Selected Reasons for This Selection

Institution

In a multicenter collaborative study, variations among enrolled patients and subtle differences in treatment methods between facilities are anticipated to potentially influence EMR outcomes.

2.Pretreatment biopsy (presence vs. absence)

Pretreatment biopsies are often performed to confirm histology. However, 24.6% of patients with preoperative biopsies may encounter non-lifting signs after submucosal injection owing to biopsy-induced fibrosis [6]. Therefore, preoperative biopsies can affect the treatment outcomes of EMR.

3.Tumor size (<10 mm vs. ≥10 mm)

As the tumor size increases, CEMR and UEMR show lower *en bloc* resection rates [15]. For lesions measuring 5–9 mm, the *en bloc* resection rates were 95.8% and 93.3% for CEMR and UEMR, respectively. For lesions measuring 10–14 mm, the *en bloc* resection rates were 91.3% and 81.5% for CEMR and UEMR, respectively. For lesions measuring 15–19 mm, the *en bloc* resection rates were 74.4% and 62.0% for CEMR and UEMR, respectively. The maximum tumor diameter in this trial is 20 mm; therefore, a cut-off value of 10 mm was set.

4.Tumor location (bulb vs. other portions)

Gastric-type mucinous lesions are often found in the duodenal bulb, whereas intestinal-type mucinous lesions typically present in the descending part of the duodenum towards the anal side, particularly below the major papilla [20,21,22]. Gastric-type and intestinal-type adenocarcinomas differ in the frequency of submucosal invasion, which likely affects the long-term effectiveness of EMR.

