### 2.10. Sample Size Calculation

The sample size is calculated based on the primary endpoint, 1-year RFS, to assess the non-inferiority of UEMR to CEMR.

Based on previous studies, the histological complete resection rate of CEMR for SNADET is reported to be 92–100% [2,14,24]. However, these reports are all retrospective studies with relatively short follow-up durations, which could result in a lower 1-year RFS. In this trial, the 1-year RFS in the standard treatment (CEMR) group is set at 97%. Additionally, the non-inferiority margin is set at 5%. This margin was defined as the maximum acceptable absolute excess risk of recurrence at 1 year. Prior studies of endoscopic resection for SNADETs reported very low recurrence rates under standard management. In this low-event-rate setting, an absolute margin is considered clinically interpretable. The prespecified margin of 5% was determined through multidisciplinary clinical consensus, balancing a small allowable increase in recurrence risk against the anticipated procedural advantages of UEMR.

Although the significance level of the trial is typically one-sided at 0.025 [25], the probability of decision-making error in the population with tumors at 0.05 (1 out of 20) is not considered unreasonably high according to clinical trial principles. Considering that a one-sided significance level of 0.05 was accepted in previous studies on rare diseases [12], a one-sided significance level of 0.05 is set for this study. This significance level was selected to maintain statistical feasibility in a rare disease setting with an expected extremely low event rate.

Based on these considerations, assuming a 1-year RFS of 97% for CEMR and expecting UEMR to perform equivalently, with a one-sided α error of 0.05, a non-inferiority margin of 5%, and ensuring 80% statistical power, the required sample size was calculated to be 288 cases for conducting a non-inferiority test. Considering ineligible cases and an approximately 10% dropout rate, the target enrollment number was set at 320 cases.

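### Times, device cost and secondary rates are compared without stratifying by the minimisation factors: valid but mildly conservative, and free to improve

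*Protocol article*

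**What the plan says.** Section 2.5 allocates by minimisation, "incorporating four allocation adjustment factors that may influence the treatment outcomes of EMR". The list that follows names institution, pretreatment biopsy (present or absent), tumour size (<10 or ≥10 mm) and location (bulb or other), and gives a reason for each. For size the reason is numerical: "As the tumor size increases, CEMR and UEMR show lower" en bloc resection rates. From 5–9 mm through 10–14 mm to 15–19 mm, the rates are 95.8%, 91.3% and 74.4% for CEMR, and 93.3%, 81.5% and 62.0% for UEMR.

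In section 2.13.1 the 1-year RFS "will be aggregated for each group, and the intergroup difference and the 95% confidence intervals (CI) will be calculated". The secondary rates under items a and c likewise get group rates, a difference and a 95% CI. For the three times under item b the text reads: "Summary statistics will be computed for both groups. The Wilcoxon rank-sum test will be used". Device cost under item d gets the same test. None of these comparisons is stratified or adjusted.

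The factors do reappear. Biopsy, size and location define subgroup analyses in section 2.13.1. Section 2.13.3 says a post hoc multivariate analysis may be done to adjust for confounding, with no covariates named. Institution is not named in any analysis.

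**The concern.** Minimisation removes most of the chance difference between arms in the factors it balances. The crude standard error and the unstratified rank test are computed as if that difference were still free to vary. If a factor is prognostic, the stated error is therefore larger than the real one: the test rejects less often than its nominal level and loses power, and the interval covers slightly more than 95%.

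The endpoints concerned are the ones by which the article would show UEMR's practical advantages (procedure, resection and closure times, device cost, closure with standard clips) and its main short-term risk (en bloc and histological complete resection). The information needed to recover the lost precision is already recorded at allocation.

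**Working it through.** **1. The plan's own figure.** Inputs from section 2.10: "the 1-year RFS in the standard treatment (CEMR) group is set at 97"%, with UEMR assumed equal; "the non-inferiority margin is set at 5"%; "a one-sided significance level of 0.05 is set for this study"; and "ensuring 80% statistical power".

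n per arm = (1.645 + 0.842)² × 2 × 0.97 × 0.03 / 0.05² = 143.99, so 144 per arm and 288 in total; 288 / 0.90 = 320. Both stated figures reproduce, and this point does not touch them.

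**2. Primary endpoint.** Assume two equal size strata with RFS 99% and 95% (mean 97%), 144 per arm.
- Crude SE = √(2 × 0.97 × 0.03 / 144) = 0.0201.
- Within-stratum variance = (0.99 × 0.01 + 0.95 × 0.05) / 2 = 0.0287, so stratified SE = √(2 × 0.0287 / 144) = 0.0200. The ratio is 1.007.
- Actual one-sided level is 4.9%; power is 80.2% crude and 80.5% stratified.

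Over assumed strata from 98.5%/95.5% to 100%/94%, the interval is 0.4–1.6% too wide, the level is 4.7–4.9%, and the power loss is under 1 point.

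**3. En bloc resection.** The stratum rates come from the list of adjustment factors. The size mix is an assumption, because the protocol gives none. Take half of lesions <10 mm, and 70% of the larger ones at 10–14 mm.
- ≥10 mm, CEMR: 0.7 × 0.913 + 0.3 × 0.744 = 0.862. UEMR: 0.7 × 0.815 + 0.3 × 0.620 = 0.757.
- Overall: CEMR (0.958 + 0.862) / 2 = 0.910; UEMR (0.933 + 0.757) / 2 = 0.845.
- Crude variance, Σ p(1−p) over the two arms = 0.2129, so half-width = 1.96 × √(0.2129 / 144) = 7.5 points.
- Within-stratum variance = 0.2028, so half-width = 1.96 × √(0.2028 / 144) = 7.4 points.
- Ratio = √(0.2129 / 0.2028) = 1.025. Coverage of the crude interval = 2Φ(1.96 × 1.025) − 1 = 95.5%.

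Varying the share <10 mm from 30% to 70%, and the 10–14 mm share of the rest from 50% to 90%, gives an excess width of 1.1–3.7% and coverage of 95.3–95.8%.

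**4. Times.** The protocol gives no procedure times, no spread, no effect of size on time and no target difference, so every input here is assumed: 320 patients, log-normal times, log-SD 0.5 within size groups, half of lesions ≥10 mm, size multiplying time by m, and a true time 13% shorter.

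If size is perfectly balanced, the unstratified test's error is inflated by k = √(1 + 0.25 (ln m)² / 0.25) = √(1 + (ln m)²).
- Level = 2[1 − Φ(1.96k)].
- Standardised effect = −ln(0.87) / (0.5 × √(4/320)) × √(3/π) = 2.43, where 3/π is the Wilcoxon efficiency for normal data.
- Power is Φ(2.43 − 1.96k) unstratified and Φ(2.43 − 1.96) = 68% stratified.

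| m | k | Level (nominal 5%) | Power, unstratified | Power, stratified |
|---|---|---|---|---|
| 1.3 | 1.034 | 4.3% | 66% | 68% |
| 1.5 | 1.079 | 3.4% | 63% | 68% |
| 1.8 | 1.160 | 2.3% | 56% | 68% |

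Simulated minimisation (40 sites, three binary factors, assumed 0.8 biased coin) agrees. One set gave levels of 4.8%, 3.3% and 2.3%, and power of 66%, 62% and 54% against 68%, 67% and 66% for van Elteren. Across simulation runs the loss was at most 2 points at m = 1.3 and 11–12 points at m = 1.8.

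A second parametrisation (true shift 0.32 SD, no site effect) gave about 82% power for every method when the three patient factors explain 10% of the variance, and 82% against 87% when they explain 20%.

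**5. Restriction to successful resections.** Section 2.9.2 limits the times to successful resections, so fewer patients contribute and balance is only approximate. In a harsh case where success follows the en bloc rates, power for m = 1.3, 1.5 and 1.8 was 63%, 62% and 60% unstratified, against 60%, 61% and 62% with van Elteren. The gain largely disappears. Part of the crude test's rejection there arises because UEMR loses more large, slow lesions, a distortion that stratifying by size reduces. Success by the allocated method may exceed en bloc success, so the truth may lie between the two cases. Device cost covers all treated cases and is not restricted in this way.

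**The case against.** The strongest reply is that nothing here is invalid. An unadjusted comparison after minimisation is unbiased and does not inflate type I error, and the article justifies the factors as balancing variables without promising an adjusted analysis. That stands, and it makes this an efficiency point.

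It can also be said that items a and c name no CI method, so an analysis plan that is not shown could still use a stratified interval. That stands too: only the Wilcoxon test is firmly fixed by the text. Likewise, the time inputs are assumed, the loss may be close to nil, and these endpoints carry no stated power.

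A reader might go further than the documents allow in four ways:
- That the trial ignores its factors. Three define planned subgroups, and a post hoc adjustment is allowed. Neither stratifies the main comparison of arms, but neither is nothing.
- That the non-inferiority conclusion is at risk. Step 2 shows a change too small to matter.
- That en bloc and histological complete resection are tested below their nominal level. No test is planned for them, only estimates and intervals.
- That the secondary intervals are seriously wrong. The protocol's own rates give a change of about 0.2 points in a half-width of 7.5.

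What survives is that a better-matched analysis exists, uses data already held, and is better fixed now than chosen after the data are seen.

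**Conclusion.** The point holds as a minor, free improvement to the secondary analyses. The comparisons in section 2.13.1 do not use the factors the trial balances on, and where those factors are prognostic the results are conservative. For en bloc resection the excess interval width is about 1–4%, resting on the protocol's rates and an assumed size mix. For times the loss runs from almost nothing to about 12 power points, depending on how strongly size drives time. The upper end needs a 1.8-fold effect and all 320 patients, and the restriction to successful resections may shrink it. For device cost the direction is the same, but the documents support no figure. The primary endpoint is not materially affected, and the lack of stratification itself creates no false-positive conclusion.

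**What to change.** In the secondary-endpoint paragraph of section 2.13.1:
- For the three times and device cost, prespecify a van Elteren (stratified Wilcoxon) test.
- For the secondary proportions, prespecify a Mantel-Haenszel risk difference with its CI.
- Stratify both by biopsy, size (<10 vs ≥10 mm) and location (bulb vs other).
- Keep the crude results as a sensitivity analysis.

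Institution is best left out of the strata: 320 patients over 40 institutions is about 8 each.

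The cost is a sentence or two in the plan, settled before the final analysis. It needs no new data, does not change the sample size, and does not affect patients.
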